### Concealment mechanism {16b}

The randomisation list generated in the IWRS software will be concealed from staff as well as patients. Only once the patient is included in the trial, will the treatment arm be assigned to the patient by the software, and reflected in the patient’s electronic case report form (eCRF) which is only accessible by the study staff. Patients will be blinded to their allocated group up to the point that they receive the treatment—patients will be aware of whether they receive CCTA before the CTO PCI.

### Implementation {16c}

Upon enrolment, the IWRS software will automatically assign the patient to a treatment arm—CT group (A) or angiography group (B)—without any input from the study staff. As patients are enrolled in the study the next number in the randomisation list will be assigned to the patient and indicated in their eCRF.

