### Intervention description {11a}

#### Preoperative assessment

The following assessments will be performed as part of the standard of care for the diagnosis of CTO:Conventional coronary angiographyIf symptoms and viability are not established through angiography, the patient will undergo one of the following:aStress electrocardiogram (ECG)bCardiac magnetic resonance imaging (MRI)cStress echocardiographydMyocardial scintigraphyCollection of biological markers: troponin, creatine kinase, creatinine, clearance of creatinine, haemoglobin. Preoperative angiography will be performed for all patients in ambulatory settings under local anaesthesia, with either a radial artery or femoral artery approach, with the former being the first choice if the artery is of good quality. An introducer sheath measuring 4 or 5 French (Fr.) is advanced within the artery using the Seldinger technique, and a catheter is advanced through the introducer up to the heart. A 6–8 cc iodine contrast injection in the coronary artery ostia allows visualisation of coronary artery anatomy under radiography. A picture registration is obtained and archived for planning of CTO-PCI. During the procedure heparin and nitrates are administrated.

If conventional angiography indicates a J-CTO score ≥2, the patient will be enrolled in the study, if they meet the eligibility criteria. Patients will then be randomly allocated to the CT group or angiography group. Patients in the CT group will undergo an additional CCTA scan (GE CT Revolution Scan 256; Iomeron 350 iodine contrast). The total dose length product (DLP, mGy/cm^2^) and computed tomography dose index (CTDI, mGy) will be recorded. Iodine contrast for the CCTA will be 55ml (10ml saline–55ml Iomeron 350–20ml saline at 5ml/s).

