### Criteria for discontinuing or modifying allocated interventions {11b}

Treatment for some individuals that fulfilled the eligibility criteria and were allocated into the study or control group may be discontinued or modified if they present with:New disease that requires an urgent intervention which doesn’t permit antiplatelet treatment due to bleeding risk,COVID-19 infection,Septic status, orA disease that affects the patient’s autonomy.

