### Participant timeline {13}

The period of enrolment will span a 24-month period, whereas patient participation will span a 6- to 12-month period that comprise of 4 visits for the CT-scan groups and 3 visits for the angiography group (Table 2).

**Table 2 Tab2:** Participant timeline

Timepoint	Enrolment	Allocation	CT-scan	CTO-PCI	Immediate follow-up	Close-out
	D0 −30 to 180 days ± 10 days	D0 −20 to 90 days ± 10 days	D0 −1 to 30 days	D0	D0 +2 to 4 days	D0 +180 days
Enrolment:	X					
Eligibility screen	X					
Informed consent	X					
Allocation		X				
CT scan			X			
Interventions:						
Comparator (wCT)			X	X		
Control (w/oCT)				X		
Assessment						
Demographic data	X					
Clinical data	X					
Risk factors	X					
Electrocardiogram	X					
Viability/ischemia test	X					
Coronary anatomy, EF and wall motion (echocardiogram or angiography)	X					
J-CTO scoring (angiography)	X					
Blood sampling	X				X	
ACT complications					X	
Adverse events	X				X	X
Symptoms, renal failure	X				X	X
MACE					X	X
TIMI flow	X				X	X

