### Plans to promote participant retention and complete follow-up {18b}

The data for primary and secondary endpoints will be collected during CTO-PCI, and the risk of missing data is therefore small (5% max). If a patient withdraws prematurely from the study they will not be replaced, and reasons for patient withdrawal must be documented in the eCRF. For patients lost to follow-up, attempts to contact the patient must be made and documented in the patient’s eCRF.

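### The text allocates at enrolment but Table 2 allocates later; the two conflict for patients enrolled more than about 100 days before PCI, and both allow allocation well before the CT scan needs it

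*Protocol article*

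**What the plan says.** Four places in the protocol article bear on when a patient is randomised.

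- **Implementation {16c}:** "Upon enrolment, the IWRS software will automatically assign the patient to a treatment arm", and then "As patients are enrolled in the study the next number in the randomisation list will be assigned to the patient". Enrolment itself is the trigger.
- **Participant timeline {13}, Table 2:** enrolment is at "D0 −30 to 180 days ± 10 days". Allocation is a separate, later column at "D0 −20 to 90 days ± 10 days". The CT scan is placed 1 to 30 days before PCI, with no tolerance given.
- **Concealment mechanism {16b}:** "Only once the patient is included in the trial, will the treatment arm be assigned to the patient by the software". No interval is given. The arm then appears in the eCRF, which study staff can open. Patients are to remain blinded until they receive the treatment.
- **Preoperative assessment {11a}:** after enrolment, "Patients will then be randomly allocated to the CT group or angiography group". Again no interval is given.

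Three further points decide what happens to a patient lost during the wait. The intention-to-treat set and its denominator include every allocated patient, whether or not PCI takes place ({18a}, {20a}). The sample size section inflates 56 to 65 per group for under 15% withdrawal, cross-over, loss to follow-up and incomplete records together ({14}). The retention section expects at most 5% missing data, on the ground that endpoints are collected during PCI, and does not replace withdrawn patients ({18b}).

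**The concern.** The IWRS can trigger at one point only, and the article fixes two. A site that follows the text randomises at enrolment; a site that follows the table may have to wait weeks or months after enrolment.

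The timing matters because the primary outcome can arise only at PCI. A patient allocated and then lost before PCI adds to the intention-to-treat denominator and cannot have a wire crossing within 60 minutes. Counting such patients as failures shrinks the difference between arms. Leaving them out means that the exclusions arise after allocation, over a period in which staff could see the arm. The argument for at most 5% missing data rests on collection during PCI, so it does not address losses before PCI. The longer the gap between allocation and PCI, the more room there is for such losses, and nothing in the schedule shows a need for a gap of this length.

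**Working it through.** **1. Check the reading of Table 2 against a stated figure.** The article gives total participation as 6 to 12 months, with close-out 180 days after PCI.

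- From the enrolment window: 30 + 180 = 210 days to 180 + 180 = 360 days, about 6.9 to 11.8 months.
- From the allocation window: 20 + 180 = 200 days to 90 + 180 = 270 days, at most about 8.9 months.

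Only the enrolment window reaches the stated upper limit. Enrolment about 180 days before PCI is therefore intended and is not a misreading of the table.

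**2. Limits with the ±10-day tolerance (days before PCI).**

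| Step | Latest | Earliest |
|---|---|---|
| Enrolment | 30 − 10 = 20 | 180 + 10 = 190 |
| Allocation (Table 2) | 20 − 10 = 10 | 90 + 10 = 100 |
| CT scan | 1 | 30 |

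If allocation is at enrolment, it falls 20 to 190 days before PCI. If Table 2 governs, it falls 10 to 100 days before. The ranges share 20 to 100 days, where same-day enrolment and allocation satisfies both. Beyond 100 days no date satisfies both.

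**3. Distance from the CT window.** The CT scan is the only step before PCI that differs by arm. Its window opens 30 days before PCI. Allocation can therefore precede it by up to 100 − 30 = 70 days under the table and 190 − 30 = 160 days under the text.

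**4. Illustration of what loss before PCI could do.** Inputs from the article: 65 per arm, 90% versus 70%, α = 0.05, chi-squared test. Assumptions: two-sided testing, and a loss rate d before PCI that is equal in both arms. Power is exact for the Pearson chi-squared test without continuity correction: the probability, summed over both binomial distributions, that the statistic reaches the 5% critical value.

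- *Counted as failures:* the rates become 0.90(1 − d) and 0.70(1 − d), with 65 per arm.
- *Excluded:* the rates stay 90% and 70%, with about 65(1 − d) per arm.

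| Loss d | Rates if failures | Difference (points) | Power if failures | Power if excluded |
|---|---|---|---|---|
| 0 | 90% vs 70% | 20 | 83% | 83% |
| 5% | 85.5% vs 66.5% | 19 | 73% | 81% (about 62 per arm) |
| 10% | 81% vs 63% | 18 | 64% | 80% (about 58 per arm) |

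**5. What the attrition allowance covers.** Going from 56 to 65 allows (65 − 56)/65 = 13.8% of patients to leave the analysis. That offsets a smaller sample. It does not offset a smaller difference, so it answers the last column and not the one before it.

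**The case against.** The strongest reply is that this is a narrow slip of wording. Two other sections put allocation after enrolment or inclusion, in the same order as Table 2. The table's enrolment column groups screening, consent, viability testing and J-CTO scoring, so enrolment could mean the end of that phase. For patients enrolled 20 to 100 days before PCI, both versions can be met. All of this stands, and it limits the conflict to earlier enrolments. It does not remove the conflict, because the sections that agree with the table's order give no interval.

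Several stronger inferences are tempting, and the documents do not support them:

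- *Patients are routinely randomised half a year ahead.* The 190 and 100 days are outer limits, not typical values.
- *Patients know their arm throughout the wait.* The Concealment section keeps them blinded until treatment. What stands is that study staff can see the arm, and that the trial is open-label for the treating cardiologist ({17a}).
- *The intercurrent conditions listed in {11b} remove patients.* That section says only that treatment "may be discontinued or modified if they present with", and such patients remain in the intention-to-treat set.
- *The plan ignores attrition.* The sample size makes an allowance, and the retention section foresees withdrawal.
- *The power loss is as large as the failure column, or larger if the whole 15% is lost before PCI.* The allowance covers several kinds of loss together. The article does not say that patients without PCI are scored as failures; its methods section also says that missing data are considered separately for proportions. Both ways of handling them must be shown.

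It is also fair to say that the article is silent on how far ahead CT slots must be booked. A practical reason for earlier allocation may exist, but none is stated.

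**Conclusion.** The conflict is real and rests on no assumption: the Implementation section and Table 2 cannot both be followed for a patient enrolled more than about 100 days before PCI. It is also sound to say that both versions permit allocation earlier than the schedule needs, by up to 70 days (table) or 160 days (text) before the CT window opens.

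The effect on power is an illustration and not an estimate. It assumes equal loss in both arms at rates that the article does not give. For 5% to 10% loss, power lies between 73% and 64% if the lost patients count as failures, and between 81% and 80% if they are excluded, against 83% without loss. A reader might take the drop from 83% as the gain from later allocation. It is not: some patients would still be lost between a later allocation and PCI, and that remainder cannot be estimated from the article. The figures bound the risk and do not measure the benefit of the change. The change is worth making because it is specific and cheap; the documents do not show that the trial is underpowered for this reason.

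**What to change.** Reword Implementation {16c} so that enrolment and allocation are separate steps, and make Table 2 and the IWRS specification say the same. Trigger the IWRS, in both arms alike, only once the CTO-PCI date is booked and eligibility has been reconfirmed, shortly before the CT window opens. One workable limit is no earlier than about 40 days before PCI: the 30-day CT window plus 10 days for booking. This lies inside the existing Table 2 allocation window. The 10 days are a planning choice, since the table attaches its tolerance to enrolment and allocation and not to the CT scan. Patients who drop out between consent and booking would then never be randomised.

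Costs: CT appointments must be arranged within a shorter period, and the IWRS trigger must be changed. No visits or patients are added. The trial started on 1 May 2022, so the change needs an amendment with a favourable ethics opinion under {25}, and it can apply only to patients not yet allocated. The trial would then contain two allocation regimes, and the report should state the date of the switch. If the sponsor prefers not to move allocation, the minimum is to reconcile {16c} with Table 2 and state which one the IWRS follows.

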## Assignment of interventions: blinding

### Who will be blinded {17a}

This is an open-label study for the patient and treating cardiologist, but blinded for two cardiologists who will evaluate TIMI flow and residual stenosis after CTO-PCI.

### Procedure for unblinding if needed {17b}

Not applicable, as this is an open-label study.

## Data collection and management

### Plans for assessment and collection of outcomes {18a}

The following datasets will be defined:Intention-to-treat (effect of assigning the treatment): This dataset will include all enrolled patients allocated to either the CT group or the angiography group, irrespective of whether they undergo CTO-PCI, cross-over between treatment arms, or have incomplete post-intervention data.Per Protocol (effect of receiving the treatment): This dataset will include enrolled patients allocated to either the CT group or the angiography group, who undergo CTO-PCI, remain in their allocated treatment arm, and have complete post-intervention data (TIMI flow and residual stenosis available after PCI).As-treated (effect of adherence to a treatment arm): This dataset will include enrolled patients allocated to either the CT group or the angiography group, who undergo CTO-PCI, irrespective of whether they cross-over between treatment arms, and who have complete post-intervention data (TIMI flow and residual stenosis available after PCI).

The following information will be included on the eCRF after enrolment and allocation:Patients’ characteristics: age (years), sex, weight (kg), height (cm), and pregnancy test.Risk factors: smoking status, diabetes, hyperlipidaemia, hypertension, cardiovascular disease family historySymptoms related to the pathology (angina, dyspnea)Clinical/instrumental data: ECG, angiographic ejection fraction (EF), regional wall motion, ischemia, viability.Laboratory data: Troponin, creatine kinase, creatinine, clearance of creatinine, haemoglobin.Anamnestic data: previous PCI, previous CTO-PCI attempt without success, previous bypass surgery.Relevant comorbidity (renal function disease, pulmonary disease, peripheral artery disease, others), arrhythmias, allergyCoronary anatomy based on coronary angiography and to calculate the J-CTO score for all the patients. For the CT group, coronary anatomy will be reassessed with the CCTA and in addition to the J-CTO Score based on the CCTA, the CT-RECTOR and calcium scores will be calculated.

The primary endpoint, that is the success rate of difficult CTO-PCI in ≤60 min wire manipulation, will be assessed for each of the three datasets, i.e. intention-to-treat, per-protocol and as-treated, after the CTO-PCI (D0, Table 2). The TIMI flow and residual stenosis after the procedure will be recorded for each of the three datasets, i.e. intention-to-treat, per-protocol and as-treated, and will be assessed at immediate follow-up (D0 + 2 to 4 days) and final follow-up (D0 + 180 days). Laboratory parameters will be recorded for each of the three datasets, i.e. intention-to-treat, per-protocol and as-treated, and will be assessed at immediate follow-up (D0 + 2 to 4 days). The success rate of the complex CTO-PCI between both groups will be calculated for each of the three datasets, i.e. intention-to-treat, per-protocol and as-treated, at immediate follow-up CTO-PCI (D0 + 2 to 4 days) and final follow-up (D0 + 180 days). For all three datasets, i.e. Intention-to-treat, Per-protocol and As-treated, all adverse events will be recorded according to the corresponding system organ class (SOC) and preferred term (PT) using the MedDRA terminology. Creatinine levels after the CTO-PCI, summarising the renal adverse events, will be described in both groups. Symptoms (angina CCS class/dyspnea NYHA class), MACE, and renal failure will be evaluated at the CTO-PCI visit and end of study visit.

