## Statistical methods

### Statistical methods for primary and secondary outcomes {20a}

Continuous variables will be reported as means, standard deviations, medians, and ranges, whereas categorical variables will be reported as numbers and proportions. Missing data will be considered separately for the calculation of proportions. Shapiro–Wilk tests will be used to assess the normality of data distributions. For normally distributed data, differences between groups will be evaluated using two-tailed *t*-tests. For non-normal distributions, differences between groups will be evaluated using Mann–Whitney *U* tests and Kruskal–Wallis tests. Effect sizes of differences between continuous variables (e.g. TIMI flow, procedure time, etc.) will be expressed using Cohen’s d, which can be interpreted as negligible (d<0.01),very small (0.01≤d<0.2), small (0.2≤d<0.50), medium (0.5≤d<0.80), large (0.8≤d<1.20), very large (1.2≤d<2.0), or huge (d≥2.0). For categorical data, differences between groups will be evaluated using chi-squared tests. All confidence intervals will be presented two-sided with a confidence level of 95%. Denominators used to calculate ratios for the intention-to-treat analysis will be the number of patients allocated to each treatment arm irrespective if they received the allocated treatment. Denominators used in the per-protocol analysis will be the number of patients that received treatment as allocated at enrolment. Denominators used in the as-treated analysis will be the number of patients that received treatment irrespective if the treatment was allocated at enrolment. Differences in success rate (successful wire crossing in ≤60 min with TIMI flow 3 is restored and residual stenosis is <30%) will be expressed in terms of absolute risk (as well as relative risk) to determine if procedures by CCTA CTO-PCA are 20% more successful compared to procedures by conventional Angiography CTO-PCI. Likewise, differences in complications between the two procedures will be expressed using absolute (as well as relative risk). A *p* value <0.05 will be deemed statistically significant. All statistical analyses will be performed using the latest version of R (R Foundation for Statistical Computing, Vienna, Austria).

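### The per-protocol and as-treated sets used for adverse events require TIMI flow and residual stenosis after PCI, so safety summaries by treatment received could omit fatal or abandoned procedures

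*Protocol article*

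**What the plan says.** Three analysis sets are defined in the protocol article under Plans for assessment and collection of outcomes {18a}.

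- **Intention-to-treat:** every allocated patient, "irrespective of whether they undergo CTO-PCI, cross-over between treatment arms, or have incomplete post-intervention data".
- **Per-protocol:** patients who undergo CTO-PCI, "remain in their allocated treatment arm, and have complete post-intervention data (TIMI flow and residual stenosis available after PCI").
- **As-treated:** patients who undergo CTO-PCI, cross-overs included, "and who have complete post-intervention data (TIMI flow and residual stenosis available after PCI").

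The same section then places adverse events in these sets: "For all three datasets, i.e. Intention-to-treat, Per-protocol and As-treated, all adverse events will be recorded according to" MedDRA class and term. It names no other set for them. A later sentence on MACE, symptoms and renal failure gives visits but no set.

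Statistical methods for primary and secondary outcomes {20a} describes the as-treated set differently: "Denominators used in the as-treated analysis will be the number of patients that received treatment irrespective if the treatment was allocated at enrolment". Its per-protocol denominator is those treated as allocated. Neither denominator mentions available TIMI flow or stenosis. The section adds that "differences in complications between the two procedures will be expressed using absolute (as well as relative risk"), without naming a set.

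**The concern.** TIMI flow and residual stenosis are components of the primary efficacy endpoint. Requiring them is understandable for an efficacy analysis in patients with complete data. For safety it is a poor filter, because the harm itself may be the reason the measurement is absent. Outcomes {12} counts death and perforation with tamponade as MACE, and either can end a procedure before a final angiogram that can be graded.

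If such patients are removed, complication rates in the per-protocol and as-treated sets could be too low. If one planning strategy leads to more abandoned procedures, the loss could also differ between groups. These two sets are the only ones described that reflect treatment received. Sample size {14} allows for cross-over, so that view of safety may be wanted.

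**Working it through.** The plan states no figure on this point, so there is nothing to reproduce. The check sets the sections side by side and then illustrates the scale.

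**Step 1. Follow one patient through the definitions.** Take a patient who starts CTO-PCI and dies on the table, or whose procedure is abandoned, with no gradable final angiogram.

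| Set | By {18a} | By {20a} |
|---|---|---|
| Intention-to-treat | kept | kept |
| Per-protocol | excluded | kept if treated as allocated |
| As-treated | excluded | kept |

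The two sections give different answers for the per-protocol and as-treated sets.

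**Step 2. Can the data really be unavailable?** The article does not settle this. {18b} says endpoint data are collected during CTO-PCI, which favours availability. {18a} also places assessment of TIMI flow and stenosis at 2 to 4 days and at 180 days after the procedure, and a patient who dies during it reaches neither visit. Exclusion is therefore possible but not certain.

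**Step 3. Scale, as illustration only.** Inputs:

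- 65 patients per arm (Sample size {14})
- MACE of 4% and 5% in the previous randomised trial (Discussion)
- at most 5% missing data ({18b})

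Expected MACE per arm = 65 × rate: 65 × 0.04 = 2.6 and 65 × 0.05 = 3.25.

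Missing patients per arm at the stated maximum: 65 × 0.05 = 3.25.

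The tolerated missingness is about as large as the expected number of events. That does not mean the two fall on the same patients.

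If *e* of 65 patients have an event and *m* of those lack TIMI/stenosis data, the rate in the restricted set is (*e* − *m*)/(65 − *m*):

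| *e* | *m* = 0 | *m* = 1 | *m* = 2 |
|---|---|---|---|
| 3 | 3/65 = 4.6% | 2/64 = 3.1% | 1/63 = 1.6% |
| 6 | 6/65 = 9.2% | 5/64 = 7.8% | 4/63 = 6.3% |

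The row with 6 events is included because the previous trial enrolled any CTO and this one only J-CTO ≥ 2, so its rate may not transfer. The values of *m* are assumptions, since the article gives no rate of ungradable procedures.

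**The case against.** Several counter-arguments carry weight.

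- **Intention-to-treat keeps everyone.** It reports adverse events too, and Adverse event reporting and harms {22} requires every event in the eCRF. This stands. A reader might infer that serious harms disappear from the trial, and the documents do not support that.
- **Most failed procedures can still be graded.** The vessel starts at TIMI 0 and the scale has a grade for no flow. Infarction, stroke and bleeding do not by themselves prevent grading. This stands, so one cannot say that the rates *are* biased or that set membership depends on being free of harm. They *could* be biased, through the few cases without a gradable angiogram.
- **MACE is not expressly tied to the restricted sets.** This is correct. Only the adverse-event sentence names all three sets. The MACE and complications sentences name none, which leaves the set open.
- **The numbers rest on an assumed event.** This is correct. The Discussion gives cardiac deaths of 0.5% versus 0%, or 65 × 0.005 ≈ 0.3 versus 0 per arm of 65, and nothing on ungradable procedures.
- **Numerator and denominator may not actually mismatch.** A reader might infer that events vanish from the numerator while their patients stay in the denominator. That happens only if {18a} is used for one and {20a} for the other. Under {18a} alone both lose the patient, and under {20a} alone neither does. What stands is that the sections disagree.
- **A safety set may exist in the full protocol.** The abbreviation list contains one, and an article condenses. Its absence from the body is therefore not held against the plan. The point rests on what the article does state: the three sets and the adverse events assigned to them.
- **A scanned patient who never reaches PCI is a different case.** The requirement to undergo CTO-PCI excludes that patient, whatever the TIMI/stenosis condition says. This is correct, and such patients need separate handling.

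**Conclusion.** The concern holds in a limited form. {18a} applies an efficacy-data condition to two of the three sets in which it reports adverse events, and {20a} defines the denominators of those sets without it. Under {18a}, a patient with a fatal or abandoned procedure and no gradable final angiogram could leave the only safety summaries by treatment received, which could lower those rates.

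The size is unknown. At the cited 4% to 5% MACE there would be about 3 events per arm, so even one exclusion would be visible. This assumes that the earlier trial's rate applies here and that at least one event patient has no gradable result. The documents do not show that such exclusions will occur, that they would differ between groups, or that any harm is lost from the intention-to-treat report.

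**What to change.** 1. Reconcile the per-protocol and as-treated definitions in {18a} with the denominators in {20a}, and state which population each uses.
2. Remove the TIMI/stenosis condition for all safety summaries. It can remain for efficacy.
3. Report adverse events, complications and MACE in intention-to-treat (primary for safety) and in all randomised patients in whom CTO-PCI was started, grouped by whether CCTA was received, whether or not TIMI flow and stenosis are available.
4. Report CCTA-related events separately for all scanned patients.

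Item 4 should stay separate. In a pooled set of everyone scanned or started on PCI, CT patients would enter at the scan, which Table 2 allows up to 30 days before PCI, and controls only at PCI. Scanned patients who never reach PCI would then dilute the procedural rates in one group only.

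The cost is wording in {18a} and {20a}, with no new data. The downside is a safety population that differs slightly from the as-treated efficacy population.

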### Outcomes {12}

The primary objective of this study is to compare rates of successful wire crossing in ≤60 min in complex CTO (J-CTO ≥2) among the CT group and angiography group. Wire crossing will be considered successful if TIMI flow 3 is restored and residual stenosis is <30%. TIMI flow and residual stenosis will be evaluated by a pool of two cardiologists who are not directly involved in the procedure, and who are blinded to group allocation. The TIMI flow scale is classified as Grade 0 to 3 (Table 1).

**Table 1 Tab1:** TIMI flow grades

Grade 0	No flow
Grade 1	penetration without perfusion in the distal part of the artery
Grade 2	partial perfusion, the iodine contrast goes across the obstruction and fills the distal part of the artery, but the flow and the clearance of the iodine contrast are perceptibly slower if compared to the other non-occluded segments/arteries
Grade 3	complete perfusion, anterograde flow into the distal part of the artery with rapid filling and clearance if compared to the other segments/arteries.

The secondary objectives of the study are to compare:Success rates at any timeTotal time of PCI (minutes)Time of wire crossingRate of PCI complications (Major Adverse Cardiac Events, MACE): death, coronary perforation with cardiac tamponade requiring pericardiocentesis, myocardial infarction (if elevation of troponin or creatine kinase associated with change in electrocardiogram), stroke, major bleeding with loss of haemoglobin > 3 g/dl.Radiation levels during PCI expressed as transferred kinetic energy (air Kerma, Gy), dose area product (DAP, mGycm^2^), and fluoroscopy time (minutes).Volume of iodine contrast medium administered during PCI (millilitres).Cost of the PCI (euros) CTTA (CT group) Angiography Preoperative assessment, as summarised in the material invoice of every procedure.

Renal adverse events will be assessed after diagnostic coronary angiography, CCTA (CT group only), and CTO-PCI. Clinically relevant findings (like contrast allergic reaction) will be reported as adverse events. Their relationship with the CT scan or CTO-PCI will be reported. Other symptoms, such as angina CCS class, dyspnea NYHA class, MACE and renal failure will be recorded. Biologic markers, such as troponin, creatine kinase, creatinine, clearance of creatinine, and haemoglobin, will be recorded after CTO-PCI.

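### The plan handles ordered grades inconsistently, and no stated test of CCS or NYHA class uses both the order of the classes and the class recorded at enrolment (minor)

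*Protocol article*

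**What the plan says.** Four places in the protocol article bear on this.

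- **Plans for assessment and collection of outcomes {18a}**: "Symptoms (angina CCS class/dyspnea NYHA class), MACE, and renal failure will be evaluated at the CTO-PCI visit and end of study visit".
- **Outcomes {12}**: after the list of secondary objectives, which does not contain symptoms, it adds "Other symptoms, such as angina CCS class, dyspnea NYHA class, MACE and renal failure will be recorded".
- **Participant timeline {13}, Table 2**: the row "Symptoms, renal failure" is marked at enrolment, immediate follow-up and close-out (day 180). A pre-procedure class is therefore collected.
- **Statistical methods {20a}**: "For categorical data, differences between groups will be evaluated using chi-squared tests". For continuous variables it gives t-tests or, after a normality check, a rank test: "For non-normal distributions, differences between groups will be evaluated using Mann–Whitney". It introduces effect sizes with "Effect sizes of differences between continuous variables (e.g. TIMI flow, procedure time, etc", which places TIMI grade 0 to 3 among the continuous variables. The threshold is a p "value <0.05 will be deemed statistically significant". No ordinal model and no baseline-adjusted method is named.

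No hypothesis, expected effect or power is stated for symptoms.

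**The concern.** A Pearson chi-squared test gives the same result if the class labels are shuffled. With four classes it spends 3 degrees of freedom on any kind of difference, so it can miss a consistent shift towards milder symptoms and can be significant for a pattern that is not an improvement. A rank test recovers the order but still leaves out where each patient started.

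Starting class can vary in this trial. Eligibility {10} accepts CCS ≥ 2, NYHA ≥ 2, documented ischaemia or ejection fraction < 50% as alternatives, so a patient may enter with a low class on one or both scales. Enrolment class is then a natural covariate.

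What is at stake is precision in a supporting outcome. The validity of the trial's main comparison is not affected.

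**Working it through.** **Inputs from the document.** 65 per group (Sample size {14}), 1:1 allocation, significance level 0.05, two-sided. The only power figure in the article (56 per group, 80%) concerns the primary endpoint, so there is no symptom figure to reproduce.

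**Inputs that are assumptions.** Class mix, treatment odds ratio (OR) and strength of the baseline relation. The document gives none of these.

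**Step 1: what ignoring order costs, by hand.** Assume control classes I to IV at 50/30/15/5% and a common OR of 2.

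- Cumulative control proportions 0.50, 0.80, 0.95 have odds 1, 4, 19. Doubled, these are 2, 8, 38, or 0.667, 0.889, 0.974. The CT group is then 66.7/22.2/8.5/2.6%.
- Non-centrality of chi-squared with equal arms: λ = n Σ (p₀ − p₁)² / (p₀ + p₁) = 65 × (0.0238 + 0.0116 + 0.0177 + 0.0078) = 65 × 0.0609 ≈ 3.96.
- On 3 degrees of freedom, λ = 3.96 gives power of about 35%. The rank test has nearly the same non-centrality (3.96) on 1 degree of freedom, which gives about 51%.
- The signal is the same, and about 16 points are lost to the two extra degrees of freedom.
- Expected count in class IV: 65 × (0.050 + 0.026) / 2 ≈ 2.5 per cell, so the table is sparse.

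**Step 2: simulation of order alone** (20,000 trials per cell, 65 per arm), power of chi-squared against rank test:

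| Classes in use | OR 1.5 | OR 2.0 | OR 2.5 | OR 4.0 |
|---|---|---|---|---|
| Five (35/30/20/10/5%) | 14 vs 24% | 35 vs 56% | 58 vs 80% | 92 vs 99% |
| Four (50/30/15/5%) | 14 vs 22% | 35 vs 52% | 56 vs 74% | 89 vs 96% |
| Three (50/35/15%) | 17 vs 22% | 41 vs 51% | 63 vs 73% | 92 vs 96% |
| Two (60/40%) | no gain | no gain | no gain | no gain |

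The four-class row agrees with the hand calculation. The gain shrinks again at OR 4, where both tests near their ceiling.

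**Step 3: adding enrolment class.** The model is logit P(Y ≤ j) = αⱼ + β·treatment + γ·enrolment class. Simulation at 65 per arm with an assumed four-class mix gave:

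| OR | Chi-squared | Rank | Adjusted proportional odds | Adjusted minus chi-squared |
|---|---|---|---|---|
| 1.2 | 7% | 10% | 8% | 1 point |
| 1.5 | 13% | 20% | 25% | 12 points |
| 2.0 | 35% | 48% | 55% | 20 points |
| 2.5 | 51% | 70% | 74% | 23 points |

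Type I error was held. A separate model with an underlying normal scale and shifts of 0.3 to 0.6 SD gave total gains over chi-squared of 14 to 19 points at a baseline correlation of 0.3, and 16 to 25 points at 0.5.

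**Step 4: the other route.** If CCS and NYHA follow TIMI flow to Mann–Whitney, order is already used. What remains is the gain from enrolment class: in Step 3, 25 − 20 = 5, 55 − 48 = 7 and 74 − 70 = 4 points at ORs of 1.5, 2.0 and 2.5, and none visible at 1.2.

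**The case against.** **The article never assigns CCS or NYHA to chi-squared.** This stands. A reader might infer that these classes fall under the categorical rule and that no other rule applies. The TIMI example points the other way, towards a rank test. What the text supports is that ordered grades are handled inconsistently.

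**No between-group test of symptoms is announced.** This also stands. Symptoms are recorded and evaluated but do not appear in Objectives {7} or among the secondary objectives in {12}. A reader might call symptom relief the main reason the protocol gives for treating CTO. The Background lists angina or dyspnoea alongside ischaemia and reduced ejection fraction, so that goes too far.

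**The effect may be small.** Both arms receive PCI, so CT planning would change six-month symptoms mainly through eventual success. Take the cited success rates of 93.5% and 84%, and assume class I in 50% after success and 10% after failure. Class I proportions are then 0.935 × 50 + 0.065 × 10 = 47.4% and 0.84 × 50 + 0.16 × 10 = 43.6%. The OR is (47.4/52.6) / (43.6/56.4) ≈ 1.2, where every method is badly underpowered. This stands as a limit on size, and it is why a flat loss of about 20 points, another tempting reading, cannot be taken from the document.

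**This belongs in the SAP.** Partly. The detail of an ordinal model may well sit there, and its absence here is no fault. But {20a} does state a rule for categorical data and does label an ordered grade continuous. Those statements are what need clarifying.

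**Unadjusted tests are valid.** Agreed. The point concerns efficiency and clarity, not bias or type I error.

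**Conclusion.** The point holds as a minor one. The article's only rule for categorical data ignores order, its treatment of TIMI flow contradicts a plain reading of that rule for ordered grades, and on either reading the enrolment class is collected but not used by any stated test.

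If symptoms are compared between groups, the power given up at 65 per arm is about 0 to 25 points. It is near 20 only when four or more classes are in use and the OR is about 2 or more, short of the range where all tests approach full power. At ORs of 1.2 to 1.5 it is about 1 to 12 points, and with two classes in use order gains nothing. Every one of these figures rests on assumed class mixes, effects and baseline correlations. The primary endpoint and the listed secondary objectives are unaffected.

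**What to change.** In Statistical methods {20a}, state that CCS and NYHA class at day 180 are ordinal outcomes. Each is analysed by a proportional-odds model with treatment and enrolment class on the same scale, and the common odds ratio is reported with its 95% CI. Keep chi-squared for unordered categories.

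While editing, reconcile {18a}, which places symptom evaluation at the CTO-PCI visit and end of study, with Table 2, which marks enrolment, immediate follow-up and close-out. The model depends on the enrolment value being recorded as a class.

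The cost is one sentence and reliance on the proportional-odds assumption. No new data, visits or patients are needed.
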